### 8.2.5 PRIMARY HYPOTHESIS

The following primary hypothesis can be applied:

H0: The 1o outcome (weight, etc) is equal in the intervention groups at week 26 and week 52, when controlling for the value in CID2 (adults) or CID1 (children).

vs.

H1: The 1o outcome is different in the intervention groups at week 26 and week 52, when controlling for the value in CID2 (adults) or CID1 (children).

The changes in continuously distributed variables from baseline to week 26 and week 52 within treatment groups will be tested with the paired t-test or the Wilcoxon-Signed-rank test, depending on distribution (all tests two-sided).

All categorical variables will be expressed in contingency tables and analyzed using Fisher's exact test. Survival analysis using the Kaplan-Meier plot and the log-rank test will be used to investigate time to subject withdrawal.

All null hypotheses comparing groups assume equality between the treatment groups while the alternative hypotheses assume that there is a difference (two-sided). All within-group null hypotheses assume no change from baseline to week 26 or week 52 while the alternative hypotheses assume that there is a change (two-sided).

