### **8.2.7 SAMPLE SIZE ESTIMATION**

The primary aim of the study is to investigate the long-term efficacy in terms of change in body weight from baseline to study end. The sample size for the proposed study was chosen to provide sufficient power to detect differences in 26-week weight regain (for primary participants) due to the effects of the different diets. The sample estimation is based on the difference between the intervention and control groups regarding weight change (kg) from baseline to week 26. In the null hypothesis we assume that the interventions groups 1 - 4 are of equal weight at week 26 compared to baseline, while the alternative hypothesis assumes that there exists a difference in weight between the treatment groups. By this covariate method we are able to test the change from baseline to week 26 while controlling for between-group differences in the baseline value.

It is anticipated that weight differences will be smallest between the low vs. high GI diets compared to the low protein vs. high protein diets. Hence the sample size has been calculated on the basis of a previous intervention study on GI (18), which found a non-significant difference in body weight change of 0.6 kg between groups using the unpaired t-test. We assume a 0.4 kg higher weight loss based on 6-month treatment, compared to the 10-week previous intervention study (18). Thus we consider that a weight loss difference of 1 kg is a clinically relevant weight loss and a priori we assume a SD of 2.01 kg.

When assuming a difference between control and intervention group of 1.0 kg (SD 2.5 kg), at least 80% statistical power and a significance level of 5%, N=125 participants per group are required (unpaired t-test). In this model, any effect size above 0.72 kg gives a power of more than 80%.

As most other studied variables in the study are secondary objectives and because the outcome of most of these variables are not easily comparable to previous studies due to the novel design of the study, there are no calculations on sample size for variables other than the primary efficacy parameter, which is weight change to week 26.

Thus, in terms of final outcome, it is accepted that post-hoc analysis will identify that not all measures of other primary or secondary outcomes will necessarily have had the appropriate sample size.

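### Section 8.2.7 uses two SDs (2.01 and 2.5 kg), and its claim of over 80% power above 0.72 kg is false for the SD 2.5 kg model it describes, where power at 0.72 kg is about 62%

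*Protocol*

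**What the plan says.** Protocol section 8.2.7 (Sample size estimation) takes a 1 kg difference in weight change as clinically relevant. It reaches that value by adding 0.4 kg to the 0.6 kg seen in an earlier 10-week GI study, and then says "a priori we assume a SD of 2.01 kg".

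The next paragraph begins: "When assuming a difference between control and intervention group of 1.0 kg (SD 2.5 kg), at least 80% statistical power". With a 5% significance level it concludes that 125 participants per group are required, by unpaired t-test. The sentence that follows is: "In this model, any effect size above 0.72 kg gives a power of more than 80" per cent.

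Section 8.2.5 fixes the direction of testing for group comparisons: "while the alternative hypotheses assume that there is a difference (two-sided". Section 8.2.7 also says that no variable other than weight change to week 26 has a sample size calculation. No part of the protocol explains the move from 2.01 to 2.5 kg.

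**The concern.** The 0.72 kg sentence directly follows the SD 2.5 kg calculation and refers to it as its model. A threshold of 0.72 kg with 125 per group looks too small for an SD of 2.5 kg and about right for 2.01 kg, which suggests that two calculations were merged.

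This matters because it is the protocol's stated sensitivity for its only powered endpoint. Section 8.2.7 expects the GI contrast to give the smallest weight differences and bases the sizing on a GI study that found 0.6 kg. Effects somewhat below 1 kg are therefore the ones for which a reader will look to the power statement. Anyone reading a non-significant comparison of two arms against that statement would believe an effect just above 0.72 kg had less than a 20% chance of being missed. Under the SD used to size the trial, the chance at 0.72 kg is about 38%.

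**Working it through.** **Inputs.** From section 8.2.7: SD σ = 2.01 or 2.5 kg, n = 125 per group, 5% significance, unpaired t-test, 80% power. From section 8.2.5: two-sided. Groups are taken as equal in size and, to begin with, all 125 per group as analysed.

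**Formulas.** The standard error of the difference is SE = σ√(2/n). The normal approximation gives power ≈ Φ(δ/SE − 1.96) and a detectable difference at 80% power of (1.96 + 0.842) × SE. The t-test values below come from the noncentral t distribution and differ only slightly.

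**Reproducing the protocol's 0.72 kg.** With σ = 2.01:
- SE = 2.01 × √(2/125) = 0.2542 kg.
- Detectable difference = 2.802 × 0.2542 = 0.712 kg (t-test 0.715 kg).
- Power at 0.72 kg = Φ(2.832 − 1.96) = 80.8% (t-test 80.5%).

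The stated figure is therefore the SD 2.01 kg result for 125 per group.

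**The model the sentence refers to.** With σ = 2.5:
- SE = 2.5 × √(2/125) = 0.3162 kg.
- Detectable difference = 2.802 × 0.3162 = 0.886 kg (t-test 0.889 kg).
- Power at 0.72 kg = Φ(2.277 − 1.96) = 62.4% (t-test 62.1%).

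**Summary (t-test, two-sided 5%).**

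| | SD 2.01 kg | SD 2.5 kg |
|---|---|---|
| Power at 0.72 kg, n = 125 | 80.5% | 62.1% |
| Power at 1.0 kg, n = 125 | 97.5% | 88.3% |
| 80% detectable difference, n = 125 | 0.715 kg | 0.889 kg |
| n per group for 0.72 kg at 80% | 124 | 191 |
| n per group for 1.0 kg at 80% | 65 | 100 |

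**Other readings with SD 2.5 kg.**
- One-sided testing: power at 0.72 kg is 73.4%, still below 80%.
- Drop-out already included in 125: the last row shows that 125 follows directly from neither SD. It would follow from 100/(1 − 0.20) = 125, but section 8.2.7 gives no drop-out rate, so the 20% is an assumption. With 100 analysed per group, power at 0.72 kg falls to 53% and the 80% threshold rises to 0.995 kg.
- Pooled arms: 125 against 500 gives 82% at 0.72 kg, and 250 against 250 gives 90%. Neither is the model described, and their 80% thresholds are 0.70 and 0.63 kg, not 0.72 kg.

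**The case against.** The arithmetic is not in dispute. The case on the other side concerns weight and consequence.

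First, the design target is 1.0 kg, and 125 per group gives at least 80% power for it under either SD. The 0.72 kg sentence sets no sample size, analysis or decision rule. This stands, and it limits the finding to the sensitivity claim and the undefined planning SD.

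Second, the calculation is for control against one intervention group, whereas Table 1 in section 4.1 is a two-by-two layout of protein and GI. A GI comparison pooled over protein levels (250 against 250) would have about 90% power at 0.72 kg with SD 2.5 kg. The protocol does not specify that test, but the point is fair: the 38% chance of a miss applies to a comparison of two single arms.

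Third, the planned analysis in section 8.2.4 is covariate-adjusted and may be more precise than the t-test. An adjusted SD of 2.01 kg from a raw 2.5 kg would need a correlation of about 0.59, since 2.5 × √(1 − 0.59²) ≈ 2.02. No correlation is stated, and the sentence setting the sample size names an unpaired t-test.

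Fourth, section 8.2 provides for 95% interval estimates, which show what the data exclude whatever SD was planned. That reduces the risk of misreading the results but does not make the planning statement true.

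Fifth, section 8.2.4 says drop-out is allowed for in the sample size and restricts the primary analysis to completers. If 125 is the number randomised, even 0.89 kg is optimistic. This stands, so any replacement figure must carry its condition.

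**Conclusion.** The concern holds. Section 8.2.7 gives two SDs without reconciling them, and its 0.72 kg statement is false under the SD of the model it is attached to. Power there is 62% instead of more than 80%, and the 80% threshold is 0.89 kg instead of 0.72 kg. These figures assume a two-sided 5% unpaired t-test with 125 analysed in each of two single arms. One-sided testing does not rescue the claim, and a drop-out reading makes it worse. The 1.0 kg target keeps 88% power at SD 2.5 kg with 125 analysed. A later analysis plan could not make the sentence true, because the protocol's own inputs contradict it. A wrong power statement for the only powered endpoint should be corrected.

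**What to change.** State one SD in section 8.2.7, say where it comes from, and recompute every figure in the section from it.

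- **If 2.5 kg is kept:** remove the 2.01 kg assumption and replace the 0.72 kg sentence with: *With 125 analysed per group and an SD of 2.5 kg, power is 88% for a difference of 1.0 kg, and the smallest difference with 80% power is 0.89 kg.*
- **If 2.01 kg is kept:** delete the 2.5 kg calculation, give 0.72 kg expressly with SD 2.01 kg and 125 analysed per group, and explain why 125 is called required when 1.0 kg at 80% power then needs only 65 per group.

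In either case, say whether 125 is the number randomised or analysed, and give the drop-out rate if one is included. If fewer than 125 per group will be analysed, recompute the detectable difference for that number.

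The cost is the wording of one section. If 2.5 kg is kept, the stated detectable difference becomes less favourable (0.89 instead of 0.72 kg). No extra subjects are needed.

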## **9. ETHICAL ASPECTS**

## **9.1 ETHICS COMMITTEE REVIEW**

Prior to starting the study, the investigator will submit the study protocol with the supporting documentation to the local/regional Ethics Committee. The trial is not allowed to start until the local/regional Ethics Committee has approved the protocol, the constitution of which satisfies the local regulatory guidelines. Approval must be obtained in writing and a copy of this approval will be kept at the trial sites.

The Ethics Committee must be consulted whenever new events require a significant change in the protocol or its appendices during the study.

## **9.2 ETHICAL CONDUCT OF THE STUDY**

The study will be conducted in agreement with the relevant international conventions and declarations, including latest versions of:

- The Declaration of Helsinki.
- The Danish Central Scientific Ethical Committee, Guidelines on biomedical experiments,
- UN Convention on the Rights of the Child

The subjects will be insured via the public patient insurance.

## **9.3 POTENTIAL BENEFITS OF THE PROPOSED STUDY & SAFETY ASPECTS**

The benefits to the subjects studied in this research protocol, and to society at large, far surpass the risks. The Diogenes project will have great potential impact on future research in the development of obesity in general, and in the relationships between diet and the development of obesity in general. This study is not designed to treat an illness however subjects in the proposed research will receive several immediate benefits in addition to weight loss. The most important of these is repeated assessment and monitoring of several health factors including BMI, blood lipids, blood pressure, and body composition. The results of these assessments will be made available to the participants. Obesity is an epidemic within Europe and the information obtained from this research might help with future public health strategies and policies for the prevention of weight gain. If successful, this intervention could support the concept that higher levels of dietary protein and low GI foods can play a role in prevention of weight gain and in promotion of weight loss maintenance.

The discomfort of subjects enrolled in the intervention study is in all cases anticipated to be mild and temporary. Risks involved in participation are limited to slight discomfort related to blood sampling/injection, and in cases involving sampling of adipose tissue biopsies (adults only) may involve minor haematomas at the site of sampling. Considering the potential treatment benefits involved in securing genetic information that may lead to the discovery of obesity-relevant genes, we believe that these investigations are justified. The potential risk associated with the dietary components of the intervention study with respect to CVD and diabetes type 2 in adults will be fully addressed during the programme.

## **9.3 PARTICIPATION OF CHILDREN**

The inclusion of children in the dietary intervention is expected to produce a health benefit for the overweight members of this group in terms of weight loss or reduced weight gain. It is considered important to include the children in the intervention and investigate the diet within the whole family as some studies have demonstrated that the family based approach to body weight management is

more effective at helping overweight children to lose weight. Measurements for the children will be minimised, however it will be necessary to take some blood samples in order, in particular, to fully address the safety aspect of the diet. This will need to be performed in a sensitive manner to assure cooperation by the children and their parents. Although it is not expected that the high protein diet will pose any risk to either children or adults, nevertheless the effects of such a diet will be carefully monitored and action will be taken in the case of clinically significant AE (see Section 9.8 above). It is important to underline that the high protein diet does not provide more than 28% energy from protein, which is within the acceptable range for both children and adults (15). The Institute of Medicine have also concluded that no clear evidence supports that a high-protein diet increases the risk of CVD or damage to kidneys or bone (15). No adipose tissue biopsies will be taken from children.

Any observed AE during the study (this applies to both children and adults) will be reported to the Ethical Officer in the Project Board and action will be taken based on the decisions taken by the Project Board.

## **9.4 SUBJECT INFORMATION AND CONSENT**

Informed consent must be sought and given freely by each adult subject after being fully informed both verbally and in writing of the course and the aims of the study, effects and possible side effects and risks of study participation. Separate consent forms will be supplied for the sub-studies (subgroup a and b), accompanied by the appropriate explanatory literature. The subject involved must have legal capacity to give consent, must be able to exercise free power of choice and must be provided with a fair explanation of all material information concerning the study.

The subject will be given information on the possibilities of compensation and treatment in case of injury or incapacity attributable to his/her participation in the study. She/he will be assured that the consent may be cancelled and that it is possible to withdraw from the study at any time.

The subject should be told that the participation in the study is confidential, but the subject should be made aware that this participation might be disclosed to a Regulatory Authority.

Both the subject and the investigator will sign the consent form. The subject information consent form should be provided for the subject, a copy being included as an appendix to this protocol.

Informed consent for children under 18 y must be procured from the person(s) having custody. If both parents have custody, consent must be obtained from both of them. Consent must also be obtained from the child itself, if this is not excluded by circumstances. An assessment will be made as to whether the child is mature enough to understand what the experiment involves and what consent means. Even so, the experiment may not be conducted if the child objects to it. If a child is unwilling to undergo (one of) the investigative procedure(s), the investigation will be cancelled, despite initial approval by the parents. The parents will be informed about this in advance and have to agree with this behavioural code. Parents can withdraw their approval of the study of their child(ren) at any moment. A trial subject who is unable to give informed consent is to be informed and be included in a discussion of the experiment to the extent that the subject understands the experimental situation, unless this may harm the subject concerned. In the main, children from the age of 12 and up will be able to meet these requirements. However, a specific assessment must always be made.

## **9.5 SUBJECT RIGHTS TO TRIAL RESULTS**

On the informed consent form, subjects will be able to specify their choice to receive information about genetic markers or findings which may indicate potential or actual health risk. Subjects will be offered counselling if required.

## **9.6 SUBJECT PRIVACY**

The investigator affirms and upholds the principle of the subject's right to protection against invasion of privacy. All source documents and other study related documents will be treated as confidential and will be identified by treatment number, case record form number, subject initials and date of birth. The investigator will hold any information seen as confidential and will not reveal it, except when required by law.

## **10. SCIENTIFIC PUBLICATION**

Scientific publication is primarily the responsibility of the DiOGenes Publications Working Group. Authorship will be included according to the Vancouver Declaration. Reports will be published in relevant international and national peer-reviewed scientific journals, non-scientific journals or other relevant media.

## **12. SUBJECT REIMBURSEMENT**

No remuneration will be paid to trial subjects for their participation in the dietary intervention. However, reimbursement of travel expenses in certain circumstances may be considered.

